### Data entry and quality control of data

All clinical data will be recorded in the case report form. Researchers must fill in the case report form. Any corrections will be explained in the appended notes signed and dated by the physicians. Supervisors will check each case report form to make sure that the trial data are recorded in a timely manner, accurately and completely. Data input will be done separately by two data collectors with computers. The data manager will examine the data in the database to confirm that it is consistent with the data in the case report form and run a database consistency check.

### Security

Possible adverse events due to acupuncture, such as discomfort, sweating, hematoma, fainting, severe pain, and metal allergy symptoms, will be recorded by the researcher.

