### Objective

The purpose of the present study is to demonstrate the efficacy in pain relief and safety of acupuncture in patients with pelvic pain related to endometriosis.

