#### Treatment group

The design of the treatment group is guided by the theory of Traditional Chinese Medicine. Disposable, sterile, stainless-steel needles, 0.30 × 40 mm, will be inserted into the acupoints on the abdomen and legs for 15 to 35 mm. The participants assigned to the treatment group will receive acupuncture at bilateral *Sanyinjiao* (SP6), *Zhaohai* (KI6), *Taichong* (LR3), *Qichong* (ST30) and at *Guanyuan* (CV4) for a total of nine needles see (Table 1) [13]. After insertion, all acupuncture needles will be stimulated manually by rotating the needle quickly with the thumb and forefinger to evoke the needle sensation (*De Qi*) once every 10 min.

**Table 1 Tab1:** Acupuncture points

Point	Localization	Muscle	Muscle innervation
*Guanyuan* (CV4)	3 cun caudal to umbilicus	Fibrous tissue, linea alba	Th12
*Sanyinjiao* (SP6)	3 cun proximal to the medial malleolus	Musculus flexor digitorum longus, tibialis posterior	L4–5,S1–2
*Taichong* (LR3)	Depression between the first and second metatarsals	Musculi interossei dorsales	S2–3
*Zhaohai* (KI6)	Depression below the medial malleolus	Abductor of toes	L4–5, S1–2
*Qichong* (ST30)	5 cun caudal to umbilicus, 2 cun proximal to the anterior median line	Obliquus internus abdominis	Th12, L1

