#### Control group

The control group will receive acupuncture at non-acupoints. Disposable, sterile, stainless-steel needles will be inserted superficially to a depth of < 5 mm on each shoulder and upper arm, without any stimulation.

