### Primary outcome

#### Pelvic pain

The primary outcome is pelvic pain that include dysmenorrhea, intermenstrual pain and dyspareunia. They will be assessed on a VAS scale [14]. On the VAS scale, a 100-mm horizontal line from no pain on the far left to the worst possible pain on the far right is scored by determining the distance from the far left to the edge of the mark made by the patient. The distance represents pain intensity. The VAS will be assessed at baseline, the first, second and third menstrual cycles and the follow-up period. See Table 2 for the study design schedule.

**Table 2 Tab2:** Study design schedule

Period	Inclusion	Treatment			Follow-up		
Visit	1	2	3	4	5	6	7
Menstrual cycle	0 month	1	2	3	4	5	6
Patients	√						
Inclusion and exclusion criteria	√						
Informed consent	√						
Physical examination	√			√			
Medical history	√						
Comorbidities	√	√	√	√	√	√	√
VAS	√	√	√	√	√	√	√
EHP-30	√			√			√
MPI	√			√			√
BDI and POMS	√			√			√
PGIC	√			√			√
Pain diary	√	√	√	√	√	√	√
Patient compliance				√			√
Reasons for dropout or withdrawal				√			√
Adverse events				√			
Safety evaluation							√

*BDI* Beck Depression Inventory, *EHP* Endometriosis-specific quality of life, *MPI* Multidimensional Pain Inventory, *PGIC* Patient Global Impression of Change, *POMS* Profile of Mood States, *VAS* Visual Analog Scale

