## Discussion

This trial is a randomized, multi-center, placebo-controlled clinical trial and aims to demonstrate the efficacy of acupuncture as pain relief in patients with pelvic pain related to endometriosis. When acupuncturists twirl, lift and thrust needles to obtain *De Qi* in the treatment group, patients will have a feeling of burning, numbness, swelling and pain. These are normal physiological reactions [23]. It is also very important to choose the proper time for acupuncture, and we choose to initiate the intervention the week before the expected menstrual onset, three times a week. This can regulate *Qi* and blood [24], to achieve the goal of pain reduction. During the menstrual period, patients will receive acupuncture every day, when they are having pain, in order to alleviate the pain.

In addition, our study also includes an assessment of quality of life, and this is a strength of the present study. Increasing numbers of studies have shown that most patients with pelvic pain related to endometriosis have depression and anxiety, which influence their quality of life [25, 26].

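### The one sentence on recording adverse events ties them to acupuncture, and De Qi pain is called normal in the only arm that gets it, so the wording allows safety capture to differ by attribution and by arm

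*Protocol article*

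**What the plan says.** The Objective section names the "safety of acupuncture in patients with pelvic pain related to endometriosis" alongside pain relief.

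Security is a single sentence: "Possible adverse events due to acupuncture, such as discomfort, sweating, hematoma, fainting, severe pain, and metal allergy symptoms, will be recorded by the researcher". The phrase that defines what is recorded is "Possible adverse events due to acupuncture".

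Table 2 (under Primary outcome, Pelvic pain) has a row labelled "Adverse events", with no reference to cause, and a separate row for safety evaluation.

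The Discussion says of De Qi in the treatment group that "patients will have a feeling of burning, numbness, swelling and pain. These are normal physiological reactions".

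The arms differ in exactly the feature that produces these sensations. In the treatment group "all acupuncture needles will be stimulated manually by rotating the needle quickly with the thumb and forefinger". In the control group needles are placed superficially "without any stimulation".

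Under Randomization and blinding, the acupuncturists know the arm, while patients, data collector and statistician do not. Security gives the recording task to a researcher and does not say whether this is the blinded data collector.

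**The concern.** Two features of the wording could affect a safety comparison.

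First, the phrase in Security that defines what is recorded contains a causal qualifier. The example list is open as to the type of event, but the qualifier applies to every type. Whoever follows that sentence has no instruction to enter an event that does not appear to come from needling. A view on cause formed at the moment of recording cannot be revisited later, because an unrecorded event leaves nothing to re-rate.

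Second, needle pain has two labels in the article. One is adverse event (Security); the other is normal reaction (Discussion, for the treatment group). No line is drawn between them, and the second label is available in only one arm. If it is used in practice, the count of needle-related complaints falls in the treatment arm and not in the control arm, and acupuncture looks safer than it is.

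**Working it through.** No figure is stated on this point and none can be derived, so the check is to set the sections side by side and see what each tells a site to do.

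**Inputs**

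- Security: events due to acupuncture are recorded; open list of types; discomfort and severe pain are named; no distinction by arm.
- Table 2: adverse events row, no qualifier.
- Discussion: De Qi sensations, pain included, are normal; stated for the treatment group.
- Treatment group and Control group sections: stimulation to obtain De Qi in the first, none in the second.
- Randomization and blinding: acupuncturists unblinded, data collector blinded.

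**Case 1: an event with no apparent link to needling, in either arm.** Under the Table 2 row it is an adverse event and is entered. Under the Security sentence nothing asks for it. Two sites, each following a part of the article, can act differently. Control patients are also needled, so the qualifier covers both arms. Taken alone it lowers counts in both and need not favour either.

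**Case 2: a patient reports pain or discomfort at a needle, short of severe.**

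- Treatment arm: Security makes it recordable as discomfort. The Discussion makes it a normal reaction. Both descriptions fit.
- Control arm: Security makes it recordable. The Discussion offers no second label, since De Qi is not sought.

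The same complaint thus has two possible classifications in one arm and one in the other. Deciding whether a sensation is De Qi also requires knowing whether De Qi was sought, which is knowledge of the arm.

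**Case 3: severe pain.** Security names it, without exception by arm. It is recordable in both, so the ambiguity lies below this level. No threshold between normal pain and recordable discomfort is stated.

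**Direction and size.** Case 1 can under-count in both arms. Case 2 can under-count in the treatment arm alone, which would favour acupuncture. The document gives no adverse event rate for either arm and no basis for the share of events that would be left out. Any percentage would rest on an invented capture rate, so none is given.

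**The case against.** The strongest reply is that the article fixes no filter. Security does not say that nothing else is recorded, and it describes no causality judgement before entry. It can be read as a list of expected needle-related events beside an unrestricted row in Table 2. The Discussion describes sensations; it gives no recording rule and exempts nothing. Security itself lists discomfort and severe pain as recordable in either arm. And a journal article condenses a fuller protocol, where definitions, severity grading and relatedness fields commonly sit.

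Much of this stands. The text permits selective recording; it does not prescribe it. The absence of form-level detail is not held against the article. What remains rests on words that are present: the one prose sentence on recording is framed by cause, no other sentence says events are recorded regardless of cause, and the boundary between normal and adverse needle pain is open in one arm. An unrestricted row label does not settle what counts as an event, and its difference from Security is itself a reason to align the two.

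Two stronger readings are tempting, and the document does not support them:

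- A reader might infer that worsening pelvic pain would be missed. It would not. VAS, pain diary and comorbidities are ticked at all seven visits in Table 2. The Follow-up section also has researchers watch for changes in illness, and the data entry section sends all clinical data to the case report form. These are not adverse event reports, but the information is collected.
- A reader might infer that the unblinded acupuncturists decide what is entered. Security assigns this to a researcher, whose blinding status is simply not given.

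**Conclusion.** The point holds as a defect of wording with a possible effect on a stated objective. Security, read as written, allows events to be left out by attribution. Read with the Discussion, it allows needle pain to be classified differently by arm. The second could tilt the safety comparison towards acupuncture; the first could thin the counts in both arms.

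It would go too far to conclude that the plan records only events judged related, or that it excludes needle pain in the treatment arm: neither statement is in the text. The size cannot be estimated from the document. The conclusion assumes that the full protocol does not already state a broader recording rule. If it does, the remaining task is to bring the article's wording into line with it. The primary pain analysis is not affected.

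**What to change.** Reword Security along these lines: *All adverse events, whatever the suspected cause, are recorded in the same way in both groups by the blinded data collector. Relatedness to acupuncture is rated afterwards, in a separate field.* The existing examples can stay as expected needle-related events. This also brings the section into agreement with the adverse events row of Table 2.

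Reconcile Security with the Discussion by stating how needle pain and De Qi-type sensations are recorded, with the same handling in both arms, so that the comparison does not depend on whether a sensation is called normal. Then report by arm both all events and those rated related.

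The cost is a change of wording, a small change to the case report form and somewhat more event entries. No visit is added, and the blinded data collector is already in the plan. Trial status says recruitment is under way, so the change should come soon: events not entered now are hard to recover. The date from which the new rule applies should be noted.

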## Discussion

This trial is a randomized, multi-center, placebo-controlled clinical trial and aims to demonstrate the efficacy of acupuncture as pain relief in patients with pelvic pain related to endometriosis. When acupuncturists twirl, lift and thrust needles to obtain *De Qi* in the treatment group, patients will have a feeling of burning, numbness, swelling and pain. These are normal physiological reactions [23]. It is also very important to choose the proper time for acupuncture, and we choose to initiate the intervention the week before the expected menstrual onset, three times a week. This can regulate *Qi* and blood [24], to achieve the goal of pain reduction. During the menstrual period, patients will receive acupuncture every day, when they are having pain, in order to alleviate the pain.

In addition, our study also includes an assessment of quality of life, and this is a strength of the present study. Increasing numbers of studies have shown that most patients with pelvic pain related to endometriosis have depression and anxiety, which influence their quality of life [25, 26].

### Trial status

This trial is currently in the recruitment phase.

## Abbreviations

BDI: Beck Depression Inventory
EHP-30: Endometriosis Health Profile-30
MPI: Multidimensional Pain Inventory
PGIC: Patient Global Impression of Change
POMS: Profile of Mood States
TCM: Traditional Chinese Medicine
VAS: Visual analog scale
